**Trial registration number:**

UMIN000046731.

WHAT IS ALREADY KNOWN ON THIS TOPICIn patients who had a stroke undergoing rehabilitation, promoting physical activity is positively associated with functional recovery and functional outcomes.However, the effectiveness of strategies to promote physical activity in patients who had a stroke undergoing rehabilitation has not yet been consistently reported, and thus, these strategies remain unestablished.WHAT THIS STUDY ADDSThe Activate Physical Activity for Stroke pilot randomised controlled trial will examine the safety and feasibility of a multidisciplinary intervention tailored to a patient’s individual characteristics that promotes physical activity in patients who had a stroke undergoing rehabilitation.The present study will include interventions based on comprehensive and multimodal instruction concepts, such as instructing the self-monitoring of physical activity, observing physical activity using multiperson monitor supporting, and encouraging physical activity by multidisciplinary staff.HOW THIS STUDY MIGHT AFFECT RESEARCH, PRACTICE OR POLICYThe results of the present study will provide preliminary data to test the efficacy of this intervention in a larger population.

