### Outcome measures

After enrolment, all patients wear an accelerometer on their waist belt 24 hours/day, except when bathing or changing clothes. We will use the average daily number of steps taken as an index of daily hospitalised physical activity. This will be measured by a UW-204NFC (A&D Company, Tokyo, Japan) three-dimensional accelerometer that calculates steps, total calories, calories burned and distance. Patients will wear the accelerometer for a minimum of 2 weeks and a maximum of 4 weeks.

Daily hospitalised physical activity is sent to the multiperson physical activity monitoring system (MEDICA Cloud, Funabashi, Japan) through an offline connection. Medical staff, including a physician, nurse and physical therapist, will check physical activity through the monitor (figure 2). This multiperson monitor allows medical staff to observe not only a patient’s daily physical activity level but also provides a visual graph showing the degree of an increase or decrease from the previous week, a percentage breakdown of steps taken during the week, and the average walking speed when wearing the accelerometer (figure 3).

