#### Control group

Patients in the control group only undergo the supervised rehabilitation programme. Patients in the control group will not be instructed on the methods to self-monitor physical activity and will be blinded to their physical activity. Medical staff are allowed to assist patients with walking and standing when requested. After the intervention period, a physical therapist will provide them with a visual report or feedback on their physical activity using the multiperson monitor.

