### Secondary outcomes

Secondary outcomes that are evaluated as exploratory are as follows:

Physical activity.Difference in changes in walking speed between the baseline and after the intervention.Difference in changes in Short Physical Performance Battery (SPPB) between the baseline and after the intervention.Six-minute walking distance (6MWD).Difference in changes in Functional Independence Measure motor function (FIM-M) between the baseline and after the intervention.Differences in SEPA changes between the baseline and after the intervention.

We define physical activity as the number of steps taken during the last 7 consecutive days of the intervention period, which is planned to take 4 weeks. Even if patients are discharged within 4 weeks, we will use the number of steps taken in the last 7 days as the outcome for both the intervention and control groups as long as the patient has been wearing the accelerometer for at least 2 weeks. Physical activity is not blinded to the assessors because the accelerometer’s data synchronises with the multiperson monitor.

A baseline assessment is performed within 1 week of admission. Patients who can walk and become eligible for the study sometime after hospitalisation will undergo a baseline assessment on enrolment. A physical therapist will assess physical function, FIM-M, and SEPA. Comfortable walking speed is measured at 10 m along a 16-m walkway. A walking aid may be used if necessary at the time of the measurement. SPPB is an objective tool for evaluating lower extremity physical function.^24^ 6MWD is a submaximal exercise test used to assess functional capacity that will be performed according to the American Thoracic Society guidelines in a 30-m long straight corridor under the guidance of a physical therapist.^25^ Patients are allowed to use their usual assistive devices, and intermittent assistance for fall prevention will be provided as necessary.

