## Discussion

The ActivePAS pilot randomised trial is a multidisciplinary intervention that includes comprehensive and multimodal instruction concepts. The present study plans to focus not only on patients who had a stroke who are walking independently but also on those who are not. We hypothesise that the multidisciplinary intervention will favour hospitalised physical activity in patients who had a stroke undergoing rehabilitation. Furthermore, we anticipate that the present study will be safe and feasible because it will use a multidisciplinary intervention tailored to the characteristics of each patient.

To our knowledge, previous studies have not found significant effects on physical activity in patients who had a stroke undergoing rehabilitation.^17–19^ The interventions in these studies incorporated the self-monitoring of physical activity, feedback and goal setting but may not have adequately considered patient characteristics. In addition, these studies were mainly performed by physical therapists.^17 18^ In the present study, the physical therapist, will be the main facilitator of physical activity interventions for patients; however, other medical staff may also monitor patients’ physical activity at any time with a multiperson monitor. Atkins reported that using a pedometer alone did not improve physical activity in a subacute stroke population due to a lack of individualised targets.^19^ They included patients who had a stroke with the ability to walk a minimum of 3 m with or without a gait aid or with or without the assistance of one person. To promote physical activity in non-ambulatory patients who had a stroke, it may be necessary for medical staff not simply to encourage walking but to provide opportunities for walking or standing actively. The present study anticipates promoting physical activity because it considers previous studies' limitations and provides a comprehensive, multimodal intervention based on patient characteristics and walking ability.

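### Nothing keeps ward staff from viewing control patients' steps on the monitor, although staff observation through it is part of the intervention, so the control arm is open to contamination of unknown size

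*Protocol article*

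**What the plan says.** All of the following is in the protocol article.

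- **Outcome measures:** the device is worn in both arms ("all patients wear an accelerometer on their waist belt 24 hours/day, except when bathing or changing clothes"). "Daily hospitalised physical activity is sent to the multiperson physical activity monitoring system", and then "Medical staff, including a physician, nurse and physical therapist, will check physical activity through the monitor". The display includes a graph of the rise or fall against the previous week. Neither the data flow nor the viewing is restricted by arm.
- **Key-messages box after the trial registration number (what this study adds):** the interventions are described as including "observing physical activity using multiperson monitor supporting, and encouraging physical activity by multidisciplinary staff".
- **Discussion:** the article notes that earlier trials without a significant effect on activity were run mainly by physical therapists. As a contrast it says that here "other medical staff may also monitor patients’ physical activity at any time with a multiperson monitor".
- **Control group:** these patients receive the supervised rehabilitation programme only. They get no instruction in self-monitoring and "will be blinded to their physical activity". Staff may help them walk or stand if asked. Their data are held in the same system, because a therapist shows them their record from it once the period is over.
- **Secondary outcomes:** "Physical activity is not blinded to the assessors", because the data synchronise with the monitor. No distinction is made by arm.
- **Randomisation and blinding; Study setting:** staff know the allocation, and both arms are treated in one hospital.

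**The concern.** A controlled comparison needs each component under test to be absent from the control arm, or to be declared common to both arms. Staff observation through the monitor is neither. It is presented as part of the intervention and as something that sets this trial apart from earlier ones, yet the measurement procedure makes it available for every patient. The plan recognises that seeing step counts can change behaviour, since it hides them from control patients. It leaves open the second route, through the staff.

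If staff notice a control patient's declining graph and respond, even informally, the control arm receives some of the support being tested. The between-arm difference in steps would then probably shrink. Under Objectives, the trial is also meant to assess effects, and the key-messages box says its results will supply preliminary data for testing efficacy in a larger population. An effect estimate diluted by an unknown amount is a poor basis for that planning, and analysis cannot undo the dilution afterwards.

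**Working it through.** **1. Passages side by side.** The plan states no figure on this point, so the check is one of consistency.

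| Question | Intervention arm | Control arm |
|---|---|---|
| Wears the accelerometer | Yes | Yes (Outcome measures: all patients) |
| Data held in the monitor | Yes | Yes (Control group: feedback is given from it later) |
| Staff view restricted during the period | No | No restriction stated |
| Patient sees own steps during the period | Yes | No (Control group) |
| Self-monitoring, weekly visual feedback, standard encouragement | Yes | No |
| Step target (set, or considered once walking is independent) | Yes | No |
| Walking or stepping opportunities offered by staff to patients who need help to walk | Yes | No; help only on request |

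The third row is the gap. The component named in the key-messages box and the Discussion is not separated by arm, which does not fit the statement that controls undergo only supervised rehabilitation. The last three rows show that the components acting directly on the patient are separated.

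**2. Which outcomes are exposed.** The primary outcome (Primary outcome section) is safety and feasibility. Retention (wearing the device) and completion of the intervention hardly depend on what staff see of control patients. Steps and the other between-arm outcomes are secondary and labelled exploratory.

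**3. Illustration of size.** The inputs are:

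- From the plan: 32 patients allocated 1:1, so 32 / 2 = 16 per arm; significance level 0.05.
- Assumed: a two-sided test; a true standardised effect d of 0.8 or 1.0; a share c of the effect reaching controls of 10% to 40%. The plan states none of these and reports that no formal power calculation was done.

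The observed effect is d × (1 − c). The noncentrality of the two-sample t-test is d(1 − c) × √(16/2), on 16 + 16 − 2 = 30 degrees of freedom. For d = 1.0 and c = 0.2, the observed effect is 0.80, the noncentrality is 0.80 × 2.828 = 2.26, and power is 59%.

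| c | d = 1.0: observed effect, power | d = 0.8: observed effect, power |
|---|---|---|
| 0 | 1.00, 78% | 0.80, 59% |
| 10% | 0.90, 69% | 0.72, 50% |
| 20% | 0.80, 59% | 0.64, 42% |
| 30% | 0.70, 48% | 0.56, 34% |
| 40% | 0.60, 38% | 0.48, 26% |

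A normal approximation gives slightly higher values (81% and 62% at c = 0) and the same pattern. The planned step analysis is an ANCOVA adjusted for age, sex, NIHSS and FMA-LE. Its absolute power would differ from the t-test's, but the proportional loss of effect, c, would not.

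**The case against.** A reader might infer that the control arm is contaminated, or that one active component is delivered to both arms. The document does not support either statement.

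- Nowhere does it say outright that staff look at control patients' screens during the period, or that they act on what they see. The first is inferred from all patients being connected and no restriction being stated.
- Observation reaches a patient only through what staff then do. The steps that act on the patient (self-monitoring, goals, standard wording, weekly feedback, offered walking) are described for the intervention group alone. Passive viewing is not shown to have an effect by itself.
- Staff know the allocation, so they know whom the encouragement is meant for. Help for controls is given on request, and a request from the patient is not a reaction to the monitor.
- The figures showing the monitor and the intervention overview are not available here, and an arm-specific display cannot be ruled out.
- Steps are exploratory in a pilot without a formal power calculation, so power figures carry little weight.

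These points stand. They rule out a claim of demonstrated contamination and any stated size. They do not close the gap: the text lets staff view both arms while calling that viewing part of the intervention. The limitations in the Discussion mention bias from staff knowing the allocation, but not from staff seeing control patients' steps. They also concede that staff compliance and the frequency of the intervention cannot be ascertained, so spill-over to controls would probably go unnoticed too.

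**Conclusion.** The point holds as an exposure, not as an established fault in the control arm. One listed intervention component is not confined to the intervention arm, and masking of control step data stops at the patient. Any effect would probably bias the exploratory step comparison and the other between-arm secondary outcomes towards no difference. Its size cannot be derived from the document, which gives neither an effect size nor any basis for the share of the effect that might reach controls. The power table therefore shows sensitivity only and predicts nothing. The conclusion assumes that the monitor display is not already split by arm. It leaves the primary feasibility aims essentially intact, and is worth acting on because prevention is cheap.

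**What to change.** **Preferred.** State in Outcome measures and Control group that, during each control patient's intervention period, the ward staff's monitor view shows intervention patients only. Control data would be open only to an existing study team member not involved in that patient's care, for wear checks, and released for the feedback already planned after the period.

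**If the system cannot separate the views.** State that staff viewing is common to both arms, remove it from the components under test in the key-messages box and the Discussion, and add the contamination risk to the limitations.

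**If the display is already split by arm.** One sentence saying so is enough.

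**Cost.** The preferred option is a small set-up task, provided the system allows restricted views, which the sponsor must confirm. Ward staff would not see control patients' steps for up to 4 weeks. The fallback costs only text, but it narrows what the trial tests.

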**Figure 2 F2:**
[figure not shown]
Multiperson physical activity monitoring system and a triaxial accelerometer.

**Figure 3 F3:**
[figure not shown]
Visual feedback displayed on the multiperson monitor.

### Intervention

#### Conventional rehabilitation

Patients undergo a rehabilitation programme (≤3 hours/d) to improve ADL according to their functional disability impairment. These programmes include muscle strengthening training, balance training, standing training, walking training, ADL training, cognitive training, swallow training and speech training.

Outside of rehabilitation, patients can move around the ward and the bed based on an individualised multidisciplinary assessment of a patient’s mobility and cognitive abilities.

#### Intervention group

An overview of the interventions is shown in figure 4. We will instruct patients in the intervention group to self-monitor their hospitalised physical activity. Specifically, we plan to use the method to self-monitor physical activity previously described by Kanai *et al* and Atkins *et al*.^16 19^ Patients in the intervention group will be asked by the physical therapist to record physical activity measured with the accelerometer on an exercise calendar at the end of the day. The patient and physical therapist collaboratively set a target number of steps per day, considering the patient’s walking ability and prestroke physical activity. By sharing these physical activity goals with multidisciplinary staff, we will encourage patients to promote physical activity outside rehabilitation. The standardised wording used by multidisciplinary staff to instruct patients is ‘try to walk more than you did last week’ and ‘keep self-monitoring your steps’. The physical therapist will provide visual feedback on changes in the number of steps taken over time and goal achievement to the patient every 7 days after study enrolment using the multiperson monitor. The physical therapist praises the patient if the patient achieves the physical activity target. If the patient does not achieve the physical activity target, the physical therapist will discuss a modified physical activity target with the patient by viewing the multiperson monitor display. With the instructions for self-monitoring physical activity and the multidisciplinary intervention, patients will be expected to improve their self-efficacy for physical activity (SEPA) and adopt other positive health behaviours.

**Figure 4 F4:**
[figure not shown]
Overview of interventions.

We will instruct patients on the same self-monitoring methods, even if they need supervision or slight assistance to walk. However, we encourage walking and standing outside rehabilitation through multidisciplinary intervention to promote physical activity for these patients. For example, we provide patients with the opportunity to walk to the bathroom or dining room with medical staff at least once a day and stepping activities (such as stepping and forward stepping) at the bedside or by the chair. If these patients can walk independently during the intervention period, we will also consider setting a physical activity target as described above.

#### Control group

Patients in the control group only undergo the supervised rehabilitation programme. Patients in the control group will not be instructed on the methods to self-monitor physical activity and will be blinded to their physical activity. Medical staff are allowed to assist patients with walking and standing when requested. After the intervention period, a physical therapist will provide them with a visual report or feedback on their physical activity using the multiperson monitor.

### Primary outcome

The primary outcome of the present study is to examine the safety and feasibility of the multidisciplinary intervention. Outside of rehabilitation, we track and record all adverse events, such as falls, trauma requiring treatment, and neurological deterioration. An independent assessor (MN) will assess the number of adverse events during the intervention. To examine the feasibility of the multidisciplinary intervention, we will assess the retention rate (wearing the device during the intervention period) and the completion rate of the intervention. In addition, we will confirm the percentage of participants who meet the eligibility criteria throughout the study.

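### As written, the primary safety outcome omits adverse events during rehabilitation sessions, where harm from the intervention could also appear

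*Protocol article*

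**What the plan says.** The Primary outcome section states: "The primary outcome of the present study is to examine the safety and feasibility of the multidisciplinary intervention". It then says where harm is counted: "Outside of rehabilitation, we track and record all adverse events, such as falls, trauma requiring treatment, and neurological deterioration". An independent assessor "will assess the number of adverse events during the intervention". The abstract gives the same outcome simply as adverse events, with no limit on setting. Table 1 lists safety at weeks 1 and 4 and does not mention setting.

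The excluded time is described under Conventional rehabilitation: "Patients undergo a rehabilitation programme (≤3 hours/d) to improve ADL according to their functional disability impairment". Its content is also given: "These programmes include muscle strengthening training, balance training, standing training, walking training, ADL training, cognitive training, swallow training and speech training". Both arms receive this programme, and the Control group section describes it as supervised.

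Physical activity is measured on a different window. Under Outcome measures, "all patients wear an accelerometer on their waist belt 24 hours/day", apart from bathing and changing clothes. The step outcome under Secondary outcomes covers the final week and does not remove steps taken in therapy.

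On follow-up, the intervention is planned for 4 weeks, but Secondary outcomes provides for shorter stays ("Even if patients are discharged within 4 weeks"). Accelerometer wear may last from 2 to 4 weeks.

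**The concern.** The collection rule follows where the intervention is delivered, not where its harms could show. The intervention encourages more walking and standing on the ward. Fatigue from that could plausibly lead to a fall in the next balance or walking session. Neurological deterioration, which the rule names as an event, can begin anywhere. Read literally, the rule leaves both out of the primary outcome when they happen in therapy.

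The trial's main conclusion is at stake. A finding that the intervention is safe would be read, as the abstract invites, as covering all adverse events, when it covers only those outside sessions. The limit also falls on what is collected, so an analysis plan cannot restore events that were never entered in the trial data.

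**Working it through.** The article gives no event rate, no split of events by setting and no distribution of stay, so there is no plan figure to reproduce. The target of 32 patients was set without a formal power calculation and does not bear on this point, except that 1:1 allocation gives about 16 per arm.

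**1. Does the text limit the setting?** The rule opens by placing the recording outside rehabilitation. The word *only* does not appear. However, the same opening phrase is used under Conventional rehabilitation for the time patients spend on the ward between sessions, so reading it as a setting is consistent with the article's own usage. Nothing elsewhere adds in-session events.

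**2. How much time is excluded?** The input is at most 3 h/day (Conventional rehabilitation).
- Share of the whole day: 3/24 = 12.5%.
- Share of waking time, with waking hours assumed: 3/16 = 18.8%, 3/15 = 20.0%, 3/14 = 21.4%.
- Per patient over 4 weeks: 28 × 3 = 84 of 28 × 24 = 672 hours.

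These are shares of time at the 3-hour maximum. They are not shares of events missed.

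**3. What could that do to the count?** Let *f* be the share of a patient group's events that happen in sessions. The recorded share is 1 − *f*. The article gives no value for *f*. Over an assumed range of 10% to 50%, the outcome would capture 90% down to 50% of events.
- If *f* is the same in both arms, both counts shrink but their ratio is unchanged.
- If the intervention moves harm into sessions, *f* differs by arm, and the recorded ratio equals the true ratio × (1 − *f* intervention)/(1 − *f* control). As an illustration only, with *f* = 30% against 10%, the factor is 0.70/0.90 = 0.78. A true ratio of 0.90/0.70 = 1.29 would then be recorded as 1.0.

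**4. Length of observation (minor).** Sixteen patients give 16 × 4 = 64 person-weeks at 4 weeks and 16 × 3 = 48 at 3 weeks. With equal weekly risk and mean stays of 3 against 4 weeks, the expected ratio of counts is 48/64 = 0.75. Randomisation balances expected stay, so a gap of that size would need a real effect on discharge. For chance alone, with stays assumed uniform on 2 to 4 weeks in both arms, a simulation of 20,000 trials put the 95% range of the person-time ratio at about 0.87 to 1.14. For comparison, at an assumed 0.1 events per patient-week each arm expects 64 × 0.1 = 6.4 events. Poisson variation then gives a ratio range of exp(±1.96 × √(2/6.4)), about 0.33 to 3.0. Chance imbalance in stay is small beside that.

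**The case against.** The strongest reply is attribution. The arms differ only outside sessions and share the same conventional programme, so counting events where the arms differ keeps background therapy events out of a small comparison. That is a sensible reason to want an outside-rehabilitation count, and it stands. It is not a reason to leave the other events unrecorded, because a setting flag keeps the targeted count intact.

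A second reply is that the full protocol or analysis plan may say more. That is fair for denominators, repeat events and person-time, which an article commonly leaves to those documents. It does not cover the collection rule, which the article itself states.

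A reader might infer more than the documents support, in three ways:
- **That therapy time is unwatched.** The programme is described as supervised. The gap is in what enters the outcome, not in whether staff see the event.
- **That unequal stays could distort the arm comparison twofold.** A ratio of 14 to 28 days describes two individual patients. Between arms it would require essentially everyone in one arm to leave at 2 weeks and everyone in the other to stay for 4. Nor does the article say that arm totals will be compared without denominators; the 2 to 4 weeks is accelerometer wear time.
- **That events are detected more often in the intervention arm because of the 7-day feedback.** That contact is described as step feedback and goal review, not as an enquiry about adverse events. Both arms have a therapy programme, and Table 1 shows one safety schedule.

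**Conclusion.** The point holds for the setting restriction. Followed as written, the primary safety outcome omits events arising during up to 3 hours a day of standing, balance and walking training and other therapy. That is 12.5% of the day, or about 19% to 21% of waking time if 14 to 16 waking hours are assumed. The number of events lost is unknown. The conclusion rests on the literal reading of the collection rule and on carry-over of harm into sessions being plausible; the documents do not show that it occurs.

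This is a correctable weakness in how a pilot defines safety. It does not invalidate the trial. Unequal length of stay is a secondary reporting matter.

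**What to change.** Reword the Primary outcome section so that all adverse events are recorded in both arms, in any setting, from randomisation to the end of the intervention period or discharge. Give each event a flag for during or outside rehabilitation. Report the all-setting count by arm and, beside it, the outside-rehabilitation count.

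As a minor addition, give for each arm the number of patients with at least one event and the patient-days of observation, because stays may differ.

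The cost is one extra data field, a little more recording and some added events unrelated to the intervention, which the flag helps to separate. The change affects recording only, not patient care. It is best made before further data are collected, since events left out may not be recoverable later.
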